**Methods/design:**

This is a two arm non-randomised community implementation trial with a once off round of post-test follow-up per HIV positive participant to assess linkage to care in low income communities. The intervention arm is a social franchise CBCT in which unemployed, self-employed or employed community members are recruited, contracted and incentivised to test at least 100 people per month, identifying at least 5 HIV positive tests and linking to care at least 4 of them. Social franchisees receive approximately $3.20 per HIV test and $8 per client linked to care. In the control arm, full-time employed HIV counsellors conduct CBCT on a fixed monthly salary. Primary study outcomes are HIV testing uptake rate, HIV positivity, Linkage to care and treatment rate and average counsellors’ remuneration cost. Data collection will be conducted using both paper-based and electronic data applications by CBCT or SF counsellors. Data analysis will compare proportions of HIV testing, positivity, linkage to HIV care and treatment rates and counsellors’ cost in the two study arms.

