**Discussion:**

The study will provide important insight into whether the SF-delivered CBCT programme increases testing coverage and linkage to care as well as reducing CBCT cost per HIV test and per HIV positive person linked to care.

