SFs will be remunerated per specific measurable work activities done in order to track progress and measure costing of the project, while also delivering agreed outputs and maintaining the brand. As such, R40^1^ will be paid per HIV test conducted. This amount remunerates a basic package of HTS services to each client tested that includes consenting a client, conducting an HIV test, distributing condoms, providing client tailor made HIV prevention messages and relevant referrals,^2^ screening for TB and STI and subsequently making necessary referrals, documenting the client. A second, and much bigger remuneration, of R100 will be paid for every HIV positive client linked to HIV care and treatment programmes in the health system. This larger amount is aimed at motivating linkage to care which proved challenging for most counsellors implementing CBCT programmes in the country [33, 34]. SFs will be contracted to test a minimum of 100 clients per month. This minimum requirement was determined by calculating the average time required to conduct HIV testing of an average of 5 people per day while allocating time to conduct other duties including mobilisation, documentation and business management aspects. In order to motivate the SFs to study communities to identify and target HIV hotspots [35, 36], it is a contractual requirement to find at least 5 HIV positive individuals in the 100 people tested. This translates to a minimum 5% HIV positivity target in Tshwane district. The target for linkage to care was at least 4 (80%) of the 5 HIV positive clients being linked to care. Consideration was made of the challenges of linkage to care based on FPD’s experience of running the CBCT programme. The project will review the targets upwards once SFs demonstrated delivery of adequate and quality work in order to align to the UN 90–90-90 target for South Africa to link 90% of the HIV positive people identified [30, 37]. Regular (weekly, bi-monthly, monthly, and quarterly) reports, field visits and observations will be made by FPD to monitor program performance and address any challenges. FPD will audit the SFs’ work and provide regular feedback to SFs to assess their progress. The same linkage to care process as in the FPD HTS will be followed by counsellors.

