### Outcomes

The study has four primary outcomes for programme success: 1) *HIV testing uptake rate,* is defined as all clients who received a basic package of HTS, including HIV testing, divided by the total number of clients offered HIV testing multiplied by 100, 2) *HIV positivity* is defined as the number of clients testing HIV positive divided by the total number of clients tested for HIV multiplied by 100, 3) *Linkage to HIV care and treatment rate* is a proportion of all clients tested positive during the current reporting period and successfully linked to care, divided by the number of all HIV positive clients referred for linkage during the current reporting period multiplied by 100. 4) *Average Counsellors’ remuneration cost* per person tested, per HIV positive test and per person linked to care will be calculated to determine the average cost of employing counsellors in each study group per outcome described above. Secondary outcomes include 5) *App use rate,* is the total number of participants whose data were primarily captured on the app divided by the total number of clients tested multiplied by 100, 6) *First time HIV testers rate* is the proportion of persons identified as testing for HIV for the first time divided by the total number of people tested in a given period multiplied by 100, 8) *Couples HIV testing rate* is defined as the proportion of two people, identifying themselves as partners, testing and receiving results together divided by the total number of clients testing multiplied by 100.

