### Data analysis

Data will be downloaded from the database and retrieved in excel format through an export mechanism and exported to Stata [43] for analysis. The analysis of primary outcomes will be conducted by comparing proportions of HIV testing, positivity rates, linkage to HIV care and treatment rates, app use rates and per counsellor cost by gender and age group in the two study groups. Descriptive statistics will be performed to describe the data. Proportions stratified by age group and gender will be calculated and presented. In comparing proportions between FPD and SF, 95% confidence intervals will be calculated and presented. All analyses will be conducted using STATA 14.0. A costing analysis will be done to assess programme cost per counsellor per HIV test, positivity and linkage to care.

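### The Data analysis section words the primary cost comparison in two ways, and neither is the cost outcome defined under Outcomes (counsellor pay per person tested, per positive and per person linked)

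*Protocol article*

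**What the plan says.** Three places in the article describe the cost measure.

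- **Outcomes**, fourth primary outcome: average counsellor remuneration "per person tested, per HIV positive test and per person linked to care will be calculated to determine the average cost of employing counsellors". The numerator is counsellor pay, and there are three output denominators.
- **Data analysis**, the sentence on the primary outcomes: "app use rates and per counsellor cost by gender and age group in the two study groups". The denominator is the counsellor, split by gender and age group.
- **Data analysis**, last sentence: "A costing analysis will be done to assess programme cost per counsellor per HIV test, positivity and linkage to care". The numerator is now programme cost. The output denominators return, but the counsellor stays in the expression.

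The abstract's Discussion paragraph gives the question to be answered: whether the franchise model succeeds in "reducing CBCT cost per HIV test and per HIV positive person linked to care". The summary that closes the main Discussion also lists pay per test among the outcomes.

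The arms are paid differently. In the intervention arm R40 "will be paid per HIV test conducted", and a second payment "of R100 will be paid for every HIV positive client linked to HIV care and treatment programmes". Control counsellors receive a fixed monthly salary that is not necessarily tied to output (Control arm section). Its amount is not given.

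**The concern.** Cost is one of four primary outcomes, and lower unit cost is a conclusion that the trial means to draw. A plan that names three different cost quantities leaves open which one supports that conclusion.

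The choice is not neutral here. Under piece-rate pay, cost per counsellor rises with output while cost per test hardly moves. Under a fixed salary, cost per counsellor is constant and cost per test falls as output rises. A per-counsellor comparison therefore partly measures how much each franchisee worked, not what a test cost.

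A counsellor is also not the same unit in both arms. Table 2 gives control staff an eight-hour day and sets franchisees no limit on hours or days.

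The numerator matters too. Programme cost can include items that pay does not. Control teams drive out from the office each day (Control arm section), and the main Discussion expects difficulty in estimating travel costs.

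Finally, if gender and age group are client characteristics, as for the other measures in that sentence, a fixed salary per counsellor has no natural split by them.

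**Working it through.** **Inputs from the article.** Franchise pay is R40 per test and R100 per linked client (Intervention arm section). The abstract has the same rates in dollars: "Social franchisees receive approximately $3.20 per HIV test and $8 per client linked to care". The contract minimums are 100 tests a month, 5% positive and 80% of positives linked. There are 19 counsellors per arm, each with at least 100 clients a month (Sample size section). The control salary S is not stated.

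**Step 1: the plan's own figures.** 2 arms × 19 counsellors × 100 clients × 24 months = 91,200, or 45,600 per arm, as the Sample size section states. The two pay scales agree: 40/3.20 = 12.5 and 100/8 = 12.5 rand per dollar. The article gives no cost figure for either arm to reproduce.

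**Step 2: franchise pay.** For T tests a month at the contract yields, links = 0.05 × 0.80 × T = 0.04T. Pay = 40T + 100 × 0.04T = 44T.

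| Tests a month | Pay per counsellor-month | Per test | Per positive | Per link |
|---|---|---|---|---|
| 100 | R4,400 | R44 | R880 | R1,100 |
| 150 | R6,600 | R44 | R880 | R1,100 |
| 200 | R8,800 | R44 | R880 | R1,100 |

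The quantities defined under Outcomes do not change with volume. Pay per counsellor doubles from 100 to 200 tests.

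**Step 3: when the two rankings differ.** Let control counsellors do C tests a month at salary S, and franchisees T tests.

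- Franchise cheaper per test: 44 < S/C, so S > 44C.
- Franchise dearer per counsellor: S < 44T.

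Both hold when 44C < S < 44T, which requires T > C. If C > T, the mirror case arises between 44T and 44C: the franchise arm is cheaper per counsellor but dearer per test.

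**Step 4: numbers, with assumed volumes.**

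- C = 100, T = 150: rankings differ for S between R4,400 and R6,600 ($352 to $528).
- C = 100, T = 200: S between R4,400 and R8,800 ($352 to $704).
- C = T = 100, the planning figure: both limits are R4,400, the window is empty, and the rankings always agree.

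Example for C = 100, T = 150, with an assumed S = R5,500. Per test it is R44 against R55, so the franchise arm is 20% cheaper (11/55). Per counsellor it is R6,600 against R5,500, so the franchise arm is 20% dearer (1,100/5,500).

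The same window applies to cost per positive and per link only if the control arm has the same yields, which is a further assumption.

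**The case against.** The strongest reply is that the per-output comparison is not absent. The last sentence of Data analysis carries the test, positive and linkage denominators, and the Outcomes section, the abstract and the closing summary all express cost per output. On that view the per-counsellor phrase is loose shorthand for an outcome whose title mentions counsellors' remuneration. That is a plausible account of the intent, but it does not settle the text. The last sentence keeps the counsellor in the expression and replaces pay with programme cost, so no sentence of the analysis section states the defined quantity.

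A reader might infer that the plan will rank the arms the wrong way round. The article does not support this. A reversal needs unequal volumes and a salary inside a window, and the planning volume is the same in both arms. Unequal volumes are plausible, because the planning figure is a floor ("SFs will be contracted to test a minimum of 100 clients per month"), but the article does not show them.

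A reader might also infer that the last sentence means averaging counsellor-level ratios, and that this would inflate cost in the control arm alone. The section never says that ratios will be averaged, and the one-sided claim fails for two of the three measures. Franchise cost per link is 100 + 40 × tests/links, which is convex in link yield; cost per positive likewise varies with yield. For example, take two franchisees with 100 tests each and 4 and 8 links (assumed). They cost R1,100 and R600 per link, a mean of R850. The ratio of totals is (4,400 + 4,800)/12 = R767, so averaging inflates the franchise figure by about 11%.

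Lastly, the choice of estimator and interval method is detail that an article may leave to a fuller document. That is fair. The finding rests on the conflicting definitions, not on the missing detail.

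**Conclusion.** The concern holds as an internal inconsistency on a primary outcome. The first cost measure in Data analysis has the wrong denominator. The second has a different numerator and an extra per-counsellor term. This conclusion needs no assumption.

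The consequence is conditional. Because one arm is paid by output and the other by salary, cost per counsellor does not answer the abstract's question about unit cost. It could order the arms differently from cost per test if volumes differ: with 150 against 100 tests a month, for control salaries between R4,400 and R6,600. That range rests on assumed volumes and on franchise yields at the contract minimums. No reversal is shown, and at equal volumes there is none. No direction of bias is established either.

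**What to change.** In Data analysis, replace both cost phrases with one statement of the primary cost comparison. For each arm, divide total counsellor remuneration by total persons tested, by total HIV positive tests and by total persons linked. Give the between-arm difference in each with a 95% confidence interval that treats the counsellor as the unit, for instance by resampling counsellors.

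Label pay per counsellor as descriptive. Label any wider programme cost as secondary and list the items that it includes. Drop the gender and age split for cost, or say how pay is to be allocated to client groups.

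The cost is a change of wording. The primary comparison uses the pay and output records that the outcome already requires, and counsellor identity codes are already in the database. Making the change before the cost results are seen also removes the freedom to choose among measures that could favour different arms.

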## Discussion

The study seeks to test the efficacy of the SF-delivered CBCT programme to increase HIV testing coverage and linkage to care. To our knowledge, this is the first community-based HIV testing and counselling study to contract social franchisees for HIV testing and linkage with the goal to increase HIV testing and treatment in the population. We believe that the results will be informative not only in Africa, but beyond. If found to be efficacious, the study may have a crucial influence on policy and implementation of CBCT as a public-private sector response to HIV prevention. Findings may also contribute towards an evidence base for community health workers’ contribution in relieving the health burden. The intervention may be an effective implementation tool for reaching first time testers and the hard to reach populations at high risk of HIV infection including men, young people and members of the key populations such as MSM, FSWs, and IDUs. This is because the SFs, who are recruited from and deployed to work in the same community have a better understanding of the local HIV hotspots that they then targeted with HIV testing. In addition, the intervention’s data App may influence the way CBCT programmes can be run with respect to the health information system. This is because the App facilitates effective use of personal health data. Lastly, the intervention may influence the way CBCT and similar health projects should be conducted while strengthening grassroots community health workers, unemployed and self-employed people as social franchisees. In a country where unemployment has reached 27% the training and employment of unemployed local people for SF-CBCT creates better life opportunities.

Our study design has some strengths and limitations. The strengths of the design include that it compares a new model of SFs with existing CBCT approach that has been implemented for over a decade now [14]. That the CBCT approach has been successfully implemented in at least three years offers a good standard of care to compare a new implementation programme, SF, with. The site of the implementation of the study, Tshwane district in Gauteng province, was a good selection for two main reasons. Firstly, Gauteng has an HIV prevalence similar to the national average rate. Secondly, the study sites consisted of rural, urban and peri-urban centres which is comparable to the South African population at large. In addition, the sites also contained heterogeneous populations including foreigners, local indigenous people as well as internal migrants from across other provinces. This population heterogeneity favours the generalisation of the study findings to the greater South African population for the purpose of HIV prevention through testing and treatment. Also, that the population is predominantly black African mirrors the populations that bears the brunt of the HIV pandemic in the country.

However, the fact that the two models will be implemented in the same communities (not cluster based) and that communities and clients are not randomised is a limitation for the study. Only an analysis by individual client level is possible due to non-randomisation. There may be challenges in conducting an economic analysis of costs as getting appropriate estimates of travel in the sub districts as both FPD and SFs counsellors conduct testing in the same sub-districts. On the other hand, not restricting counsellors to specific areas in the study area also enable counsellors to assess hotspots and testing in the areas of choice each day.

We anticipate challenges in linkage to care among the SF CBCT. This is because as independent businesses or self-employed, though using an FPD brand, they may not be as well accepted at health facilities as FPD employees would. Although clients usually live within a walkable distance to the local health facilities, some clients may face challenges in accessing these facilities due to shortage of transport money or experiencing stigma making them unable to visit the facility or choosing to visit facilities far away from their locality to minimise stigmatising situations. Training of CHWs will address some of these challenges. In rare circumstances, clients may be offered transport, when available, to access health facilities. The monitoring and management staff will be available to provide support and resolve any conflicts that the SFs face during referral and linkage to care processes. In addition, regular contact with the franchisor through reporting of data, challenges, financial, and commodity fill up visits will enable any challenges to be addressed during project implementation. The use of the App on tablets in a community, sometimes rural or peri-urban communities, raises challenges of internet connection and or gadget battery flat outs or insecurity/theft in high crime areas leading to completing data on paper and later capturing onto the electronic database with possible challenges related to data completeness and real time availability.

The trial will inform on the importance of health information system including gathering, processing, sharing and storage. The success of linkage to care is also hinged on collecting reliable identifying, tracking and locating information. A relationship of trust, which is governed by the consenting process, helps to obtain such private information [44] for follow-up purposes. As observed in large health information systems in South Africa, missing data is a challenge [45, 23]. In our study, missing data may be a result of the interviewer not strictly observing prompts or personnel capturing data from paper-based forms missing some values while capturing. Refresher training and close monitoring of the project will minimise missing data. One of the strengths of the app is that it has prompts that require the counsellor to respond to compulsory questions before proceeding to the next questions.

We also anticipate challenges in data accuracy, completeness, quality assurance and verification of testing of clients. Similar challenges have been reported in an evaluation of social franchisees in the health provision in developing countries [46]. Nevertheless, our monitoring system through site visits, data verification and auditing process, and integrating databases with the national department of health to facilitate linkage to care will, among other things, help to deal with such challenges.

In summary, the trial seeks to recruit, train and equip unemployed, self-employed and employed community members to increase community-based HIV testing and treatment. The programme data will help to generate evidence of success or failure of the SF CBCT approach based on the programme outcomes including HIV uptake, positivity, linkage to care rates and remuneration cost per test. The trial is unique in that it uses the social franchise approach to increase coverage of HIV testing and treatment and at the same time creating employment opportunities for unemployed people and provides free training and support in business management. The SFs will receive skills that they will use beyond the project life span. The study results will inform the Franchisor of potential limitations to the programme and ways to circumvent those challenges going forward. The results will also inform the South African Department of Health and the funding organisations on new and effective approaches to increase HIV testing and treatment including identifying at high-risk populations and the hard to reach population with HIV testing. The results are awaited by key stakeholders including the donors, policy makers and researchers.

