## Methods

### Design

The study is a two arm non-randomised community implementation trial with a once off round of post-test follow-up per HIV positive participant to assess linkage to care. Clients will be tested by one of the HIV testing strategies – either by an existing FPD counsellor or a SF HIV counsellor under the sub-contracted model. Each study arm has 19 counsellors conducting CBCT. The overall study design is illustrated on Table 2.

**Table 2 Tab2:** Process flow for the FPD and Social Franchise HTS

Item	Activity	FPD	Social franchise
1. Counsellor Recruitment and contracting	Contract	1. Employed by FPD 2. Normal employment contract 3. Normal payroll contract 4. Work for 8 h a day	1. Unemployed, self-employed or employed elsewhere, not employed by FPD 2. Contracted by franchisee-franchisor contract 3. No restriction on hours, days worked 4. Test >/= 100 people per month 5. Test>/5 HIV + tests per month 6. Link >/= 4 HIV + clients per month
	Remuneration	1. Fixed monthly salary	1. Paid $3.20 per HIV test 2. Paid $8 per HIV + client linked
	Training	Training focussed on: 1. Pre-test, test, post-test, documentation, referral and linkage to care	Training focussed on: 1. Pre-test, test, post-test, documentation, referral and linkage to care 2. business development & management
2. Mobilisation	Community level mobilisation	Community events; flyers; campaigns (e.g. couples counselling); conducting systematic door-to-door mobilization campaigns distributing flyers, and condoms	Community events; flyers; campaigns (e.g. couples counselling); conducting systematic door-to-door mobilization campaigns distributing flyers, and condoms
	Individual level mobilisation	Informing households on the benefits and availability of testing for HIV; scheduling household level testing appointments and/or actively recruiting clients for same day HTS	Informing households on the benefits and availability of testing for HIV; scheduling household level testing appointments and/or actively recruiting clients for same day HTS

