### Sample size and sampling

Based on current rates of the CBCT programme, which were used to come up with targets for the SF model, data will be analysed after 12 months of programme implementation. Each arm will have 19 counsellors recruiting at least 100 clients per counsellor per month for 12 months excluding weekends and holidays. Requiring counsellors to test 100 clients per per month is a conservative assumption that considers SFs as new players in conducting CBCT to emphasize accuracy and quality in CBCT work. Based on this assumption and calculation, a total of 91,200 participants are expected to be recruited in 24 months and half of these (45,600) will be recruited by SFs while the other half by FPD. A 12-month follow up and a final 24 months evaluation to assess programme effectiveness will be conducted. No randomisation of counsellors or clients will be done. All sub districts were selected based on current rates of HIV infection, which is highest in the townships where predominantly black Africans reside.

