### Control arm - FPD HTS

In order to identify people infected with HIV (PLHIV) and bring them into HIV care, FPD designed and implemented a CBCT programme in 2013 that ran through 2018 [29]. The programme aimed to make significant inroads towards the UNAIDS’s 90–90-90 goal [30] through the alignment with the South African Government’s (SAGs) National Strategic Plan on HIV, STIs and TB (NSP 2012–2016) [31] and the PEPFAR/SA HIV Prevention Strategy [32]. To implement the CBCT strategy, FPD formally advertised and employed counsellors to conduct HTS. The counsellors attended a 10-day training programme covering HTS and linkage to HIV care including documentation, approaching communities, consenting as shown on Table 2. FPD managed counsellors’ daily HTS activities and remunerated them monthly without necessarily pegging the salary to HTS outputs. The client recruitment strategy for testing is described as home-based in which counsellors moved door-to-door recruiting clients in the community. FPD teams, who include a driver/counsellor and at least four other counsellors per team, drive from the office to the communities in the selected study/project sites daily to conduct HIV testing and travel back to the office. Counsellors will test and refer clients for linkage to care. Linkage to care will be confirmed by checking clinic registers and Tier.net, an electronic patient management system used for capturing patient-level data on HTS, pre-ART and ART services. Counsellors will follow up clients for up to six months to ensure that they are linked to care.

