
**Fig. 1 Fig1:**
[figure not shown]
Picture showing the Mobile App data entry form designed for this study

The app will be accessible through using an assigned password to each counsellor. Each counsellor will have a user name/identity (ID) code which reflects in the database to assist programme managers to track progress per counsellor, per day. Data will be captured and saved automatically onto the app and in real-time transferred to the cloud-based database using an internet connection. In cases of limited or no internet connection, the app saves an encrypted copy of the data on the tablet/device and the counsellor then uploads the data manually, through the push of a single button, onto the database when the internet connection becomes available. Counsellors conduct manual uploads at the end of each working day to ensure all data are uploaded onto the database. After development, the App was tested and data were captured, retrieved, analysed and compared for completeness, validity and accuracy.

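### Non-randomisation does not prevent allowing for clustering by counsellor; 95% CIs that treat clients as independent would be too narrow, by an amount that depends on the outcome and the ICC

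*Protocol article*

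**What the plan says.** The limitations paragraph of the Discussion fixes the level of analysis and gives the reason: "Only an analysis by individual client level is possible due to non-randomisation". The Data analysis section adds: "In comparing proportions between FPD and SF, 95% confidence intervals will be calculated and presented". It names no variance method. Nowhere does the article mention correlation among clients of one counsellor, an ICC, a design effect, robust standard errors or a random effect.

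The structure of the study is set out elsewhere. Under Design: "Each study arm has 19 counsellors conducting CBCT". Under Sample size and sampling: "Each arm will have 19 counsellors recruiting at least 100 clients per counsellor per month for 12 months excluding weekends and holidays", and "a total of 91,200 participants are expected to be recruited in 24 months and half of these (45,600) will be recruited by SFs". The same section says: "No randomisation of counsellors or clients will be done". The text after Figure 1, in the data collection section, says: "Each counsellor will have a user name/identity (ID) code which reflects in the database".

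**The concern.** A client's arm is decided by which counsellor does the test. The thing being compared, a franchise contract paid by output against a salaried post, is applied to counsellors and not to clients. Counsellors can be expected to differ in skill, effort and choice of clients. The Intervention arm section builds some of this in, because each franchisee decides daily where to test and whom to target, and is paid per test and per linkage. Outcomes of one counsellor's clients are therefore likely to be correlated.

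Lack of randomisation does not stop the analyst from allowing for this, so the Discussion sentence gives a wrong reason for a restriction. The restriction also sits badly with the rest of the plan: counsellor remuneration is a primary outcome, the Data analysis section includes cost per counsellor, and control-arm pay is a fixed salary per counsellor.

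An analyst who follows the text literally would compare two proportions with tens of thousands of supposedly independent clients per arm. Chance differences between counsellors could then be reported as precise differences between the two models, in a study meant to inform roll-out.

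**Working it through.** **1. The plan's own figure.** 2 arms × 19 counsellors × 100 clients × 24 months = 91,200, and 19 × 100 × 24 = 45,600 per arm. Both agree with the protocol. Over 12 months the product is 45,600 in total (22,800 per arm), so 91,200 rests on 24 months. It is a recruitment product; no effect size, power or ICC enters it.

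**2. Inputs.**
- Clusters: 19 counsellors per arm (Design).
- Clients tested per counsellor: m = 1,200 at 12 months, 2,400 at 24 months (Sample size and sampling).
- Positivity p = 5%, and linkage p = 80%: the franchisees' contractual minimum and target (Intervention arm), applied to both arms as an assumption.
- Positives per counsellor: 5 a month, so m = 60 at 12 months and 120 at 24 months, giving 19 × 120 = 2,280 per arm.
- ICC: not in the document. Assumed range 0.001 to 0.05, with equal cluster sizes.

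**3. Formulas.** Naive half-width = 1.96 × √(2p(1−p)/n), with n per arm. Design effect DE = 1 + (m−1) × ICC. Factor by which the naive interval is too narrow = √DE. Between-counsellor SD = √(ICC × p(1−p)). Using t on 36 df (2.028) in place of 1.96 multiplies the clustered width by a further 1.035.

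**4. Positivity at 24 months, ICC 0.01.** Naive: 1.96 × √(2 × 0.05 × 0.95 / 45,600) = 0.28 points. DE = 1 + 2,399 × 0.01 = 24.99, and √DE = 5.0. Clustered half-width 1.41 points, or 1.41 × 1.035 = 1.46 with t. Effective n per arm = 45,600 / 24.99 ≈ 1,825. The naive 95% interval would cover about 30%.

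**5. Linkage at 24 months, ICC 0.01.** Naive: 1.96 × √(2 × 0.8 × 0.2 / 2,280) = 2.32 points. DE = 1 + 119 × 0.01 = 2.19, and √DE = 1.48. Clustered half-width 3.44 points, or 3.44 × 1.035 = 3.56 with t. Coverage of the naive interval about 81%.

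**6. Range over the assumed ICC** (factor √DE; SD between counsellors in points):

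| ICC | Positivity SD | Factor, 12 mo | Factor, 24 mo | Linkage SD | Factor, 12 mo | Factor, 24 mo |
|---|---|---|---|---|---|---|
| 0.001 | 0.69 | 1.48 | 1.84 | 1.26 | 1.03 | 1.06 |
| 0.005 | 1.54 | 2.64 | 3.60 | 2.83 | 1.14 | 1.26 |
| 0.01 | 2.18 | 3.60 | 5.00 | 4.00 | 1.26 | 1.48 |
| 0.05 | 4.87 | 7.81 | 11.0 | 8.94 | 1.99 | 2.64 |

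At 24 months a factor of 2 needs an ICC of only 0.00125 for positivity, but 0.025 for linkage. A factor of 3 needs 0.0033 and 0.067 respectively.

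**7. Consequence for the second year.** At ICC 0.01 the clustered half-width for positivity is 1.44 points at 12 months and 1.41 at 24. Doubling the clients adds almost nothing when the number of counsellors stays at 38.

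**8. Uptake.** Its denominator is clients offered testing, a number the document does not give. It is at least as large as the number tested, so at a given ICC the factor is at least that for positivity. No interval is calculated, because no uptake rate is stated.

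**The case against.** Four points on the other side have force.

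- **The variance method is not stated.** A reader might infer that the plan's intervals definitely ignore clustering. The Data analysis section does not say so, and a condensed article may leave the method to a fuller document. What stands against this is that the one sentence fixing the level of analysis gives a wrong reason, and nothing else in the article allows for counsellors.
- **The Discussion sentence may mean something narrower.** It follows a remark that both models run in the same communities, so it may only rule out a community-cluster analysis. A GEE or mixed model with counsellor as cluster is itself a client-level analysis. The sentence therefore needs correcting, but it does not force the error.
- **The size is not uniform.** A reader might conclude that every interval will be several times too narrow. That rests on an assumed ICC and fails for linkage, a primary outcome. Comparisons within gender and age group have smaller clusters. With ten strata, as an illustration, m = 240 gives √(1 + 239 × 0.01) = 1.84 for positivity and m = 12 gives √(1 + 11 × 0.01) = 1.05 for linkage, at ICC 0.01.
- **Some supporting facts have limits.** Counsellors are not tied to areas, so a shared location is a weaker source of correlation than it might seem. The counsellor ID is described with app access; the document does not say that paper forms recaptured later carry it.

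The control arm may tempt a reader further: "FPD teams, who include a driver/counsellor and at least four other counsellors per team". Since 19 / 5 = 3.8, there would be at most three full teams. That is too few for a reliable team-level analysis, and the document does not say that team membership is recorded.

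**Conclusion.** The concern holds in conditional form. Non-randomisation is not a reason to confine the analysis to clients, and still less to treat them as independent. If the intervals are computed that way, they will be too narrow whenever the ICC is above zero. For positivity the understatement is substantial even at small ICCs; for linkage it is modest at ICC 0.01 and reaches a factor of about 2.6 only at ICC 0.05. These figures rest on assumed ICCs, equal cluster sizes, and the franchisees' 5% and 80% targets applied to both arms.

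The documents do not support a flat claim that the intervals ignore clustering, or a single false-positive rate: no variance method, significance test or ICC is given. Nor would allowing for clustering deal with confounding from the non-randomised comparison, which the protocol acknowledges as a limitation.

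**What to change.** 1. **Discussion:** correct the sentence on level of analysis. Say that counsellors and clients are not randomised, so confounding remains possible, and that client outcomes will be analysed with allowance for clustering by counsellor.
2. **Data analysis:** state that all arm differences and 95% CIs account for clustering by counsellor, by one prespecified method. Either use counsellor-level summaries (19 against 19, t on 36 df), or a GEE or mixed model with standard errors clustered on counsellor ID and a small-sample correction for 38 clusters.
3. **Reporting:** give the estimated ICC for each outcome expressed as a proportion.
4. **Data capture:** make sure the counsellor ID is carried onto records captured on paper and entered later.

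A team-level sensitivity analysis is not recommended.

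The cost is a change of wording, a routine analysis option, and a check that the ID field is complete on paper-captured records. The intervals will be wider, most of all for positivity and uptake.
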